## Abstract

**Background:**

Road crashes continue to pose a significant threat to global health. Young drivers aged between 18 and 25 are over-represented in road injury and fatality statistics, especially the first six months after obtaining their license. This study is the first multi-centre two-arm parallel-group individually randomised controlled trial (the FEEDBACK Trial) that will examine whether the delivery of personalised driver feedback plus financial incentives is superior to no feedback and no financial incentives in reducing motor vehicle crashes among young drivers (18 to 20 years) during the first year of provisional licensing.

**Methods:**

A total of 3,610 young drivers on their provisional licence (P1, the first-year provisional licensing) will participate in the trial over 28 weeks, including a 4-week baseline, 20-week intervention and 4-week post-intervention period. The primary outcome of the study will be police-reported crashes over the 20-week intervention period and the 4-week post-intervention period. Secondary outcomes include driving behaviours such as speeding and harsh braking that contribute to road crashes, which will be attained weekly from mobile telematics delivered to a smartphone app.

**Discussion:**

Assuming a positive finding associated with personalised driver feedback and financial incentives in reducing road crashes among young drivers, the study will provide important evidence to support policymakers in introducing the intervention(s) as a key strategy to mitigate the risks associated with the burden of road injury among this vulnerable population.

**Trial registration:**

Registered under the Australian New Zealand Clinical Trials Registry (ANZCTR) - ACTRN12623000387628p on April 17, 2023.

**Supplementary Information:**

The online version contains supplementary material available at 10.1186/s12889-023-16886-z.

## Background

Road crashes are predicted to be the fifth leading cause of death worldwide by 2030 [1]. Despite early successes in reducing the burden of road injury, road crashes remain a leading cause of mortality and morbidity in Australia [2]. Over the past decade, there have been no significant declines in the rate of road deaths and serious injury [2]. Consequently, an urgent rethink of road trauma prevention measures is needed if Australia is to achieve its national road safety targets of reducing fatalities by 50% and serious injuries by 30% by 2030 [3].

Approaches to reducing road deaths and serious injury must account for the overrepresentation of young drivers in road crashes. Road injury is one of the leading causes of death among young Australians, accounting for 1 in 5 deaths among people aged 15–24 [4, 5]. Despite only comprising 14% of all licence-holders, young drivers are involved in one-quarter of all serious crashes and remain over-represented in crash statistics, with the risk of a crash being greatest in the first year of a young driver’s licensure [5, 6].

The FEEDBACK trial builds on past research indicating that feedback and financial incentives can reduce risky driving behaviours [7, 8]. Some studies found that personalised safety feedback to drivers led to improved driving behaviours, like reducing speeding and harsh braking [9–12]. Others suggest that feedback alone may be insufficient to motivate behaviour change, and that feedback should be combined with financial incentives in order to deliver significant reductions in risky driving [8, 13–15]. Stevenson et al. [8], for example, found that the effects of feedback alone did not yield statistically significant reductions in risky driving behaviours, whereas feedback combined with low-cost financial incentives had a significant effect.

Similarly, providing financial incentives cannot be assumed to improve driving performance. Although there is evidence that financial incentives can motivate behaviour change – like smoking cessation, physical activity, vaccination, and screening [16, 17] – the effects of such incentives do not always generate the intended outcomes [7, 18, 19]. Instead, incentives can create unintended consequences whilst doing little to influence the behaviour of already-safe drivers [7, 20, 21]. For instance, Mortimer et al.’s [7] study found that providing and withdrawing an incentive completely offset the gains in driving performance while the incentive was ‘switched-on’, leaving affected drivers worse off than they started. These studies underscore the instrumental role of careful incentive design.

The FEEDBACK trial will use ‘smart incentives’: low-cost, loss-framed incentives that are personalised based on the drivers’ behaviour. Studies aiming to reduce traffic congestion [22–24], improve drivers’ fuel efficiency [25], and modify commuters’ travel behaviours [26, 27] all highlight the utility of offering personalised incentives – rather than static rewards to trigger behaviour change. Whereas previous studies have provided penalties (or rewards) whenever the incentivised behaviour fell beneath a *fixed* threshold [8], thresholds for incentives in the FEEDBACK trial will be driver-specific and set to require (achievable) improvement relative to previous driving behaviour. These driver-specific thresholds will be progressively lowered – month on month – to incentivise further improvements, even among safer drivers.

Incentives in the FEEDBACK trial will leverage loss-aversion by imposing monthly penalties for risky driving, rather than rewards for safe driving [28]. Penalties will be framed as deductions from an upfront payment to address differences in acceptability between rewards and penalties. This approach mimics a Pay-As-You-Drive (PAYD) implementation, where financial penalties are typically implemented as periodic deductions from an earned discount on PAYD insurance premiums [29, 30].

Whilst previous research indicates that feedback and incentives can improve driving behaviours [7, 8, 28], this study will also evaluate the likely impact of personalised feedback and incentives on crash risk specifically. Moreover, this trial marks the first time that such an intervention will be evaluated among young drivers in their first year of licensing in relation to crash outcome. This evaluation will provide policymakers with crucial evidence on the effects of population-scale interventions, such as insurance premiums being linked to safer driver behaviours.

## Methods and design

### Overview of the study design

The FEEDBACK trial is a two-arm parallel group, superiority randomised controlled trial. The study was approved by the Human Research Ethics Committee of the University of Melbourne (HREC 023-25244-42050-4), the Queensland University of Technology Research Governance and Integrity team (Project ID: 7478) and the University of Western Australia (2023/ET000616). It was funded by the National Health and Medical Research Council Australia Partnership Grant (NHMRC; Grant number: 2,015,470). The trial was prospectively registered with Australian New Zealand Clinical Trials Registry (ANZCTR; ACTRN12623000387628p).

The trial was designed to comply with Standard Protocol Items: Recommendations for Interventional Trials (SPIRIT) [31] and Good Clinical Practice guidelines. Trial findings will be reported in accordance with the Template for Interventional Description and Replication (TIDier) checklist [32] and Consolidated Standards of Reporting Trials (CONSORT) guidelines [33].

Following NHMRC guidelines, a trial Data Safety and Monitoring Committee (DSMC) will be established. The DSMC will be a multidisciplinary group who will have no involvement in the trial nor any conflicts of interest. It will include individuals with scientific expertise in transport safety research, statistics, and a consumer representative to ensure end-user representation and engagement during the trial. The committee will convene once per year to monitor the efficacy and safety of the trial. The responsibility of the committee will be to consider reasons for ineligibility and non-participation, adherence to protocol, intervention fidelity, study events, adverse events (those perceived to be related to the devices such as smartphones), withdrawals and deaths, and provide recommendations to the chief investigator about continuing, modifying, or stopping the trial. There are no planned interim analyses or stopping guidelines.

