#### Aims and eligibility criteria

The FEEDBACK trial will examine whether personalised driver feedback and personalised financial incentives are superior to *no* personalised driver feedback and incentives in reducing motor vehicle crashes among drivers aged 18–20. To participate in the trial, drivers are required to meet the following eligibility criteria. Additionally, they will need to provide informed consent and complete an online survey that includes questions on demographic characteristics, their driving experience, and attitudes towards driving.

Aged 18 to 20 years when joining the trial.Live in one of three Australian states: Queensland (QLD), New South Wales (NSW), or Western Australia (WA).Hold a provisional (P1) licence for a car.Have access to a vehicle with Bluetooth functionality that they drive regularly.Have a smartphone that is an Android or an iPhone 6 or newer.

When consent has been provided, participants will receive a link to download a smartphone application (‘FEEDBACK’ app), developed by industry partner Urban Analytica (UA) Pty Ltd and will be asked to pair the smartphone with their car via Bluetooth. Each participant’s driving behaviour will be monitored for 28 weeks, beginning with a 4-week baseline period.

After the 4-week baseline period, each participant will be randomised into one of two groups: (1) an intervention group that will receive personalised driver feedback and personalised financial incentive, or (2) a control group that *does not* receive personalised feedback or financial incentive. The intervention period runs for 20-weeks. The trial will conclude with a further 4-week post-intervention period. Participants will receive no feedback nor incentives during the post-intervention period but will be monitored to evaluate the persistence of the hypothesised treatment effect after the intervention ceases. The trial will conclude by asking participants to complete an online questionnaire.

In order to keep participants engaged throughout the trial, both the intervention and control groups will be entered into a weekly prize draw during the 20-week intervention period and at the end of the trial. Engagement in the trial will involve keeping location tracking for the FEEDBACK app enabled throughout the trial so that the app can collect driving data.

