**Fig. 2 Fig2:**
[figure not shown]
An overview of the FEEDBACK Trial illustrating the activities during each stage of the trial: 4-week baseline, 20-week post-randomisation (intervention) and 4-week post-intervention period

Participants can withdraw from the trial at any time but will not receive financial compensation thereafter. To withdraw, a participant can contact one of the trial coordinators via email. If a participant does not inform the trial coordinators of their withdrawal but the research team no longer receives telematics data from a participant, a research staff member will call the participant to confirm whether the participant has removed the FEEDBACK app or disabled location services and whether they still intend to participate in the trial.

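### The adverse events the DSMC considers are limited to those perceived as device-related, although the intervention is feedback plus financial penalties and the article itself places the possible harm in the incentive

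*Protocol article*

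**What the plan says.** Under Overview of the study design, the Protocol article lists what the DSMC will consider. The list includes "adherence to protocol, intervention fidelity, study events", followed by "adverse events (those perceived to be related to the devices such as smartphones), withdrawals and deaths". The term *study events* is not defined. The committee may "provide recommendations to the chief investigator about continuing, modifying, or stopping the trial", and the section adds: "There are no planned interim analyses or stopping guidelines". On frequency it says: "The committee will convene once per year to monitor the efficacy and safety of the trial".

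The Background describes possible harm from incentives: "incentives can create unintended consequences whilst doing little to influence the behaviour of already-safe drivers". It also cites an earlier study in which withdrawing an incentive cancelled the gains. The section on personalised financial incentives returns to that reversal when it justifies the post-intervention monitoring.

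Participants cannot be blinded (Randomisation and blinding). The intervention group sees scores in the app and receives messages about targets and account balance. The control group's app displays nothing (Control group).

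When telematics data stop arriving, the text after Fig. 2 says that staff will call to confirm "whether the participant has removed the FEEDBACK app or disabled location services and whether they still intend to participate in the trial".

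**The concern.** An adverse-event definition should cover the plausible harms of what is being tested. Here the smartphone is only the means of delivery. The active ingredients are the weekly score, the monthly target and the AU$24 deduction for missing it. Limiting adverse events to those perceived as device-related leaves out the ingredient about which the article itself urges caution.

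The filter also depends on perception in a trial where allocation is known. An intervention participant has an app display, scores and penalty messages to which an event might be attributed. A control participant has a blank app. The same injury could be classed differently in the two arms. The article does not say whose perception counts, so neither the direction nor the size of any difference can be stated.

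What is at stake is the completeness of what the DSMC sees when it advises on continuing, modifying or stopping. The primary estimate is not affected.

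**Working it through.** The article gives no figure for safety monitoring, so the main check sets its passages side by side. Its only computed design figures, 3,068 participants before attrition and 3,610 after, reproduce exactly (1,534 per arm for 3% versus 1.5%; 1,534/0.85 = 1,805 per arm). The point does not rest on them.

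**Step 1: where each kind of harm would be recorded.**

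| Event | Where it is captured | Device filter? |
|---|---|---|
| Police-reported crash | Primary outcome, through licence numbers, both arms, blind to group (Crash data) | No |
| Self-reported crash with vehicle damage | Post-trial questionnaire, both arms | No, but asked at the end and about damage, not injury |
| Worse driving, including after withdrawal of the incentive | Weekly scores and behaviours to week 28; Persistence of treatment effects | No |
| Death | DSMC list | No |
| Withdrawal | DSMC list | No |
| Non-fatal injury, hospitalisation or distress linked to feedback or penalties | Adverse event only if perceived as device-related; otherwise only if it counts as a study event or leads to withdrawal | **Yes** |

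The last row is the gap. A non-fatal injury may come from a crash that appears in the first two rows, but those rows record the crash and are not described as safety reports. The Crash data section assigns the police data to the primary hypothesis. It gives no date of retrieval and does not mention the DSMC. Study events may be meant to include crashes, but the article does not say so.

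**Step 2: the loss-of-signal call.** A driver who is injured or in hospital would also stop sending data. The call as described confirms app status, location services and intention to continue. It is presented as a check on withdrawal. No injury question is mentioned, so the article does not show that the call would identify such an event.

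**Step 3: meeting frequency against exposure (side note).** The inputs are one meeting a year, taken as every 52 weeks, and 20 weeks of intervention. Assume even recruitment over whole years.

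- Share with a meeting during their own intervention period: 20/52 = 0.385, about 38%.
- Share with none: (52 − 20)/52 = 32/52 = 0.615, about 62%.

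This is not the share who finish before any review. That share needs a recruitment length R and a first-meeting date, and the article gives neither. Assume that the first meeting is 52 weeks after recruitment opens and that the intervention ends 24 weeks after entry (4 baseline + 20). The share already finished is then min(R, 52 − 24)/R:

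| R (weeks) | Share finished with the intervention before the first meeting |
|---|---|
| 26 | 26/26 = 100% |
| 52 | 28/52 = 54% |
| 56 | 28/56 = 50% |
| 104 | 28/104 = 27% |
| 156 | 28/156 = 18% |

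**The case against.** The strongest reply is that the parenthesis qualifies one item in a list. Study events, withdrawals and deaths stand beside it without a causal filter. Crashes, the harm that matters most, are obtained for every driver blind to group. Reversal after the incentive stops is measured weekly and has its own analysis. All of this stands, and it rules out reading the article as blind to incentive-related harm.

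Three further inferences are tempting and are not supported:

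- *The adverse-event comparison will be biased by arm.* The article plans no between-arm comparison of adverse events. The parenthesis describes a committee's remit.
- *Most participants finish before any review.* Under the assumptions in the working, the share runs from 18% to 100%, and it exceeds half only if recruitment takes less than about 56 weeks. A meeting can also protect drivers who start later, because the committee may advise modifying or stopping.
- *Yearly meetings are wrong.* Frequency is a trade-off in a low-risk trial. Ad hoc meetings and escalation between meetings commonly sit in a charter, which is not shown.

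The objection does not remove the wording itself. The article states the device restriction expressly, so this is not a detail left to a fuller document, and the restriction does not fit the article's own account of where harm may arise.

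**Conclusion.** The concern holds in a limited form. As worded, the adverse-event category is aimed at the device, while the intervention and the caution in the Background concern feedback and incentives. A non-fatal harm of that kind has no assured route to the DSMC. It depends on an undefined term, on withdrawal, or on someone perceiving a link to the phone. Crashes and deaths are captured without the filter, but nothing in the article says that crash data reach the committee while the trial is running.

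The number of events that would be missed cannot be estimated from the article. The 62% describes only how often an annual meeting falls outside a driver's own 20 weeks, under even recruitment over whole years and meetings exactly 52 weeks apart. It adds context to the wording problem and does not show that review comes too late. The sample size, the primary analysis and the crash outcome are unaffected.

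**What to change.** 1. In Overview of the study design, remove the device filter for non-fatal injury and hospitalisation. Record these in both arms whatever their perceived cause, with relatedness to device, feedback or incentive as a separate field. Deaths need no change, because the filter does not apply to them.
2. Define *study events*, and state that they include crashes reported to the DSMC during the trial.
3. Add one question on injury or hospitalisation, worded identically for both arms, to the post-trial questionnaire and to the loss-of-signal call. Report response by arm, because completing the questionnaire releases the remaining account balance in the intervention group but only a draw entry in the control group.

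The cost is a change of wording, one extra item in two existing contacts, and slightly more event recording in a low-risk trial. The sample size and the analysis models stay as they are.

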#### Aims and eligibility criteria

The FEEDBACK trial will examine whether personalised driver feedback and personalised financial incentives are superior to *no* personalised driver feedback and incentives in reducing motor vehicle crashes among drivers aged 18–20. To participate in the trial, drivers are required to meet the following eligibility criteria. Additionally, they will need to provide informed consent and complete an online survey that includes questions on demographic characteristics, their driving experience, and attitudes towards driving.

Aged 18 to 20 years when joining the trial.Live in one of three Australian states: Queensland (QLD), New South Wales (NSW), or Western Australia (WA).Hold a provisional (P1) licence for a car.Have access to a vehicle with Bluetooth functionality that they drive regularly.Have a smartphone that is an Android or an iPhone 6 or newer.

When consent has been provided, participants will receive a link to download a smartphone application (‘FEEDBACK’ app), developed by industry partner Urban Analytica (UA) Pty Ltd and will be asked to pair the smartphone with their car via Bluetooth. Each participant’s driving behaviour will be monitored for 28 weeks, beginning with a 4-week baseline period.

After the 4-week baseline period, each participant will be randomised into one of two groups: (1) an intervention group that will receive personalised driver feedback and personalised financial incentive, or (2) a control group that *does not* receive personalised feedback or financial incentive. The intervention period runs for 20-weeks. The trial will conclude with a further 4-week post-intervention period. Participants will receive no feedback nor incentives during the post-intervention period but will be monitored to evaluate the persistence of the hypothesised treatment effect after the intervention ceases. The trial will conclude by asking participants to complete an online questionnaire.

In order to keep participants engaged throughout the trial, both the intervention and control groups will be entered into a weekly prize draw during the 20-week intervention period and at the end of the trial. Engagement in the trial will involve keeping location tracking for the FEEDBACK app enabled throughout the trial so that the app can collect driving data.

### Delivery of the intervention via mobile telematics

Vehicle telematics refers to an integrated system in which telecommunications are used to transmit information captured by sensors to record real-time data about a vehicle’s operations, such as speed, acceleration, deceleration, and GPS location [34]. Applications of telematics are diverse, encompassing vehicle fleet management, vehicle diagnostics, insurance, and usage-based services [34, 35]. Furthermore, the role of telematics is gaining traction as a strategy for providing personalised feedback to drivers about crash risk indicators, which include speeding (i.e., travelling above posted speed limits) and the frequency of harsh braking and acceleration [8, 36].

While traditional telematics data collection relies on costly in-vehicle sensors, advancements in smartphone technology have enabled the capture of telematics data using low-cost smartphone sensors [37]. Furthermore, as most young drivers own a smartphone, smartphone-based telematics - hereafter referred to as ‘mobile telematics’ - presents a promising and affordable alternative for collecting telematics data from a larger population [34, 35]. Mobile-telematics technology will enable delivery of both personalised feedback and financial incentives in the FEEDBACK intervention by capturing real-time data on adverse driving behaviours that contribute to crash-related injuries such as speeding, harsh braking, and harsh acceleration.

